#### 2.5.2. Study Arms

Patients randomly assigned to the control group will receive the conventional telephone follow-up provided by primary care to COVID-19 patients and will also be able to report their symptoms 3 times a day via the healthcare application called ‘‘Home app’’, while patients randomly assigned to the active group will also receive the Bakeey E66 smartwatch and the Wellue SFS20 pulse oximeter at home. The only difference between patients who will be assigned to the experimental group and the management group is that the latter will not be provided with portable monitoring devices.

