As COVID-19 has a very broad clinical spectrum, the monitoring of the body temperature (BT), heart rate (HR), respiratory rate (RR), blood pressure (BP) and oxygen saturation (SatO2) may contribute to the early detection of clinical worsening or the occurrence of any major complications. For example, the risk of respiratory failure in the first 24 h after hospital admission based on the Quick COVID-19 Severity Index can be predicted by monitoring SatO2 and RR [11]. Similarly, alterations in certain vital signs such as BT (≥38 °C), RR (≥20 breaths per minute) and HR (>100 beats per minute) can help identify the existence of pneumonia among adult patients in primary care settings [12].

With this in mind, most studies within this line of research have used different devices to monitor each vital sign in isolation [13,14], with only a few assessing several parameters simultaneously. The latter includes one by Chung et al. [15] that used the HEARThermo device for continuous monitoring of BP and HR in patients with suspected or confirmed COVID-19 and another by Chinitz et al. [16] that used the Apple Watch Series 4 (Apple, Cupertino, CA, USA) to monitor arrhythmias and QT prolongation in COVID-19 patients in home quarantine. In addition, most of the devices that have been used for early detection of COVID-19 have been tested outside Europe [14,15,16,17,18].

One purpose of the protocol is to serve as a model for similar studies under similar conditions in order to improve pathology control. We propose to evaluate the benefit of a clinical decision support system based on: (i) the self-reporting of patient symptoms through a mobile application and (ii) the processing of data measured by wearable monitoring devices using artificial intelligence techniques in patients with COVID-19 in quarantine. All data generated will be uploaded to an online platform to which access will be provided to primary care and emergency health service professionals, allowing real-time detection of the progression of COVID-19 to severe forms and the occurrence of any potential major complications in order to promote early therapeutic interventions based on their clinical judgement. It is hypothesized that the implementation of the proposed clinical decision support system will improve the rate of detection of the clinical progression to severe forms of the disease in COVID-19 positive patients in home quarantine, compared to current practice.

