## 2. Materials and Methods

### 2.1. Study Design

Prospective, single-blind, multicenter, randomized clinical trial. Acute COVID-19 included study patients will be randomized to one of both study arms: conventional telephone calls from healthcare professionals, periodic telemonitoring with wearable devices and mobile phone application allowing self-reporting of symptoms three times a day versus traditional telephone calls from healthcare professionals and symptom reporting application.

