### 2.5. Study Overview

#### 2.5.1. Clinical Decision Support System

The clinical decision support system to be evaluated will supplement the conventional follow-up telephone call provided by primary care to COVID-19 patients (Supplementary Materials, File S2) and will consist of the following elements.

The healthcare application called ‘‘Home app’’: all patients who meet the eligibility criteria and consent to participate will be provided with access to the ‘‘Home app’’, which they can download via SMS to their mobile phone. Importantly, this application will only be compatible with smartphones running an Android^®^ operating system (Google, Mountain View, CA, USA). The application will send push notifications to the patient three times a day (10:00 a.m., 4:00 p.m., 10:00 p.m.), asking them to indicate the presence of COVID-19 related symptoms and their characteristics, and will serve as a link for sending the vital signs data measured by the wearable monitoring devices to the server, where they will be further processed using artificial intelligence techniques (only in the active group). The symptomatology covered by the ‘‘Home app’’, together with the series of clinical questions associated with each symptom, are listed in Figure 1.

Wearable monitoring devices: patients randomly assigned to the active group will receive, at home by express courier, the Bakeey E66 smartwatch (Shenzhen Yisi Technology Co. Ltd., Guangdong, China), for real-time monitoring of BT, HR and RR, and the FS20F Bluetooth Finger Oximeter (Wellue, Los Angeles, CA, USA), for self-reporting SatO2 values three times a day via the healthcare application (along with self-reporting of symptoms). Instructions will be provided to link participants, via Bluetooth, with the healthcare application and to send the monitored data to a server where it will be further processed using artificial intelligence techniques, generating moderate or severe alerts depending on whether they exceed certain pre-established values. Whenever an alarm is detected, a push notification will automatically be sent to the healthcare application, where the patient will have to answer a series of verification questions to confirm the veracity of the alarm (Figure 2).

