Patient and health professional support: the clinical decision support system (the application and wearable monitoring devices) is designed to make it easy for the patient to use, to promote patient autonomy, to make the user the center of the disease and to provide individualized health care. The application is very intuitive and the collection of vital signs will be carried out automatically, it is only necessary for the patient to have the devices in place. In case the patient needs technological support, a family member could, if desired, help to answer questions about the evolution of the development of the disease and manage the placement of the monitoring devices. In addition, patients will have access to a remote support system fourteen hours a day, via telephone contact or through an online chat in the application itself. The objective of providing remote support by qualified personnel is to promote greater patient and caregiver adherence. Furthermore, this support system can also be used by healthcare professionals to improve system management. It should be noted that the application will have a section of frequently asked questions, which will be updated and new ones will be added depending on the problems reported by patients and professionals, which will be answered employing infographics in very simple language, to favor the autonomy of the user and the healthcare professional.

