### 2.7. Data Analyses Plan

A professional biostatistician has been consulted to design the data analysis plan for the study, in which descriptive analysis of all data will be provided, including means and SDs or medians for continuous variables and proportions for categorical variables. The recorded data will be processed statistically in an encrypted form.

The statistical analysis technique to be used will be the analysis of variance (ANOVA), which will allow determining the existence of significant differences between the two groups in terms of primary and secondary outcome measures. Also, the Kaplan–Meier estimator and Cox proportional hazards model will be used to establish possible predictors of mortality and/or ICU admission. The statistical software to be used will be Stata 15 and a *p*-value of <0.05 will be assumed for statistical significance.

To assess the economic impact of the intervention on the health and social system, a cost-utility analysis will be carried out to evaluate whether there are fewer hospitalizations and calls to the emergency health service in the active group than in the control group, which translates into lower costs associated with patient care. With this in mind, an acceptability curve analysis will be carried out to see whether the proposed clinical decision support system is more appropriate than the conventional primary care telephone follow-up in terms of cost-benefit ratio.

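### The hypothesis and the economic question compare the whole system with telephone follow-up, but both arms get the app, so the trial estimates only what the devices add

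*Protocol article*

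**What the plan says.** All references are to the protocol article.

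**What is under test.** The Introduction defines the system by two components: "the self-reporting of patient symptoms through a mobile application and (ii) the processing of data measured by wearable monitoring devices using artificial intelligence techniques". Section 2.5.1 repeats this in its paragraph on support: "the clinical decision support system (the application and wearable monitoring devices". The same section says that the system "will supplement the conventional follow-up telephone call provided by primary care to COVID-19 patients" and lists the app first among its elements.

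**What it is to be compared with.** The hypothesis at the end of the Introduction is that the system improves detection of progression "in COVID-19 positive patients in home quarantine, compared to current practice". Section 2.7 plans an acceptability curve to see "whether the proposed clinical decision support system is more appropriate than the conventional primary care telephone follow-up".

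**What is randomised.** Section 2.1 gives the comparator after the description of the active arm: "versus traditional telephone calls from healthcare professionals and symptom reporting application". The Abstract and section 2.5.1 also give the app to all participants. Section 2.5.2 has controls reporting symptoms in the app three times a day and names one difference between the groups: "the latter will not be provided with portable monitoring devices", where the latter are the controls. Section 2.5.1 sends self-reported data to the online platform that clinicians consult, with no stated restriction by arm.

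**The concern.** The app is part of the intervention as the article defines it, yet the control arm receives it. The hypothesis and the acceptability curve both name a comparator without the app, and no randomised group matches that comparator.

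What is at stake is the conclusion that may be drawn. A null result could be read as showing that the whole system does nothing, when any benefit of the app is present in both arms and cancels. A positive result could be credited to the whole system over usual care, when only the devices and their alerts were tested. In the economic analysis, the control arm carries the app's costs and any effect of the app, so results labelled as a comparison with telephone follow-up would carry the wrong label.

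**Working it through.** **No figure of the plan to reproduce.** The point concerns the comparator, not a number. The target of 500 comes from a survey-precision argument in section 2.4 (a frame of 3210 patients, p = q = 0.50, coefficient 1.96). It assumes no treatment effect and has no bearing on which contrast is estimated.

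**Step 1. Is the app part of current practice?** No. Section 2.5.1 makes it an element of the system that supplements the telephone call, and the Introduction counts it as component (i).

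**Step 2. Write the contrasts.** Let R be the risk of progression under each package of care:

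- R(T): telephone calls only
- R(TA): calls plus app
- R(TAD): calls plus app plus devices with alerts

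| Source | Contrast |
|---|---|
| Hypothesis (Introduction); acceptability curve as worded (2.7) | R(T) − R(TAD) |
| Arms as randomised (Abstract, 2.1, 2.5.2) | R(TA) − R(TAD) |

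**Step 3. Take the difference.**

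[R(T) − R(TAD)] − [R(TA) − R(TAD)] = R(T) − R(TA)

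The two contrasts differ by the app's own effect. No arm is observed under T, so R(T) is not estimated, and neither is R(T) − R(TA). The same algebra holds with mean costs in place of risks.

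**Step 4. Direction.** If the app lowers risk, R(T) − R(TA) is positive and the arm difference understates the whole system's effect. If the app is inert, the two contrasts coincide. If the app did harm, the bias would reverse.

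**Step 5. Size.** The documents give no event rates and no app effect, so the size cannot be calculated. The table below only shows how the gap behaves. Every rate in it is assumed: R(T) = 10%, the full system halves the risk (R(TAD) = 5%), and the app supplies a share s of the log risk ratio, so R(TA) = 10% × 0.5^s.

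| s | R(TA) | R(TA) − R(TAD) | R(T) − R(TAD) |
|---|---|---|---|
| 0 | 10.0% | 5.0 points | 5.0 points |
| 0.25 | 8.4% | 3.4 points | 5.0 points |
| 0.5 | 7.1% | 2.1 points | 5.0 points |
| 0.75 | 5.9% | 0.9 points | 5.0 points |

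With assumed telephone-only rates of 5% and 20% and s = 0.5, the arm difference is 1.0 and 4.1 points, against whole-system effects of 2.5 and 10.0 points. Nothing in the documents favours one value of s over another.

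**The case against.** The strongest reply is that the design is a legitimate add-on comparison, openly described. The Introduction says that the study will examine differences between the active and control groups at 30 days. Section 2.7 tests differences between the two groups. The Abstract and sections 2.1, 2.5.1 and 2.5.2 all disclose that controls have the app. On this view only a label is loose, in one hypothesis sentence and one economic sentence. Most of this stands: the randomised contrast is valid and interpretable. But open description of the arms does not repair a hypothesis and an economic question that name a different comparator.

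Three stronger readings are tempting, and the documents do not support them.

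- *The economic analysis has no comparator data.* Section 2.7, in the sentence just before the acceptability curve, compares hospitalisations and emergency calls between the active and control groups. The comparator data exist; they are mislabelled as telephone follow-up.
- *Half of the system, or half of its effect, is lost.* Two components in the Introduction is a count, not a share of effect. Section 2.5.1 also lists the online platform as an element. It limits the AI processing of vital signs to the active group, and the caption of Figure 2 ties the vital-sign alerts to that group. So the device-driven alerting is inside the randomised contrast; what the arms share is symptom reporting and its upload.
- *The Conclusions repeat the error.* Section 5 speaks of the benefit of a system that includes wearables but names no comparator, so the contradiction is not there.

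It is also fair to say that, if the app helps, the error is conservative for the whole system's effect.

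**Conclusion.** The concern holds as a mismatch between the stated question and the randomised contrast. The trial can estimate the added effect and cost of the smartwatch, oximeter and their alerts over telephone follow-up plus app. It cannot estimate the app's own effect, and so cannot estimate the whole system's effect against current practice or telephone follow-up alone.

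The gap equals the app's effect, R(T) − R(TA). Its size cannot be quantified from the documents. Its direction, an understatement of the whole system's benefit, rests on the assumption that the app helps.

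A reader might infer that the trial is uninformative or invalid. That does not follow: randomisation, data collection and the comparison between arms are unaffected. What must change is the question that the comparison is said to answer.

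**What to change.** - **Introduction, hypothesis:** replace the comparison with current practice by the effect of *adding a smartwatch and pulse oximeter with alerts to telephone follow-up plus the symptom app*.
- **Section 2.7, economic question:** use the same comparator. Calculate incremental costs and effects, and the acceptability curve, against the control arm, and label that arm as telephone follow-up plus app.
- **One added sentence:** state that the trial gives no estimate of the app alone, or of the whole system, against telephone follow-up alone.

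The cost is a narrower claim and a few changed sentences; nothing in the conduct of the trial changes. Estimating the wider contrast would need a group that receives telephone follow-up alone. That is a different design and is not required for this correction.

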#### 2.5.3. Follow-Up Visit

Patient participation in the follow-up phase of the study will end when a second PCR or antigen test determines absence of virus. The final follow-up telephone visit to assess the primary and secondary outcome measures will be conducted on the 30th day after the date of the positive COVID-19 diagnosis. To minimize the risk of bias, primary and secondary endpoints will be assigned for analysis to an external endpoint adjudication committee. In addition, patients will be contacted by telephone after the end of the study to complete surveys on their satisfaction with participation in the study and usability of the ‘‘Home app’’ using the Spanish version of the System Usability Scale (SUS) [18].

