The study will examine the differences between the active and control groups 30 days after the date of diagnosis of COVID-19, in terms of clinical progression of the disease to severe forms, defined by: progression to pneumonia, need for intensive care unit (ICU) admission, need for invasive mechanical ventilation and mortality rate. On the other hand, the secondary outcomes to be considered will be: the hospital admission rate, the average hospital stay, the occurrence of major vascular events (including acute myocardial infarction, stroke and vascular death), the economic cost of the derived care to the health system, the satisfaction of professionals and patients with the project and the usability of the technologies used in the project.

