### 2.2. Eligibility Criteria

To be considered for participation in the study, patients must meet all the inclusion criteria set out in this protocol without meeting any exclusion criteria (Table 1).

All patients participating in the study will receive an SMS message on their mobile phone with a link to download the healthcare app, from which they will initially electronically sign the informed consent form required to participate in the study (Supplementary Materials, File S1) and provide their contact details and home address for delivery of the Bakeey E66 smartwatch and Wellue FS20F pulse oximeter, if randomly assigned to the active group.

When patients are discharged and their home quarantine period ends, after seven or ten days depending on symptomatology, they will be able to remove the healthcare application called ‘‘Home app’’ from their mobile phone and stop wearing the monitoring devices, although their participation in the study will not end until six months after the date of the positive PCR or antigen test, when they will receive a final follow-up call from the data monitoring board to assess the primary and secondary outcome measures.

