Integration of the system modules: Regarding primary care, health professionals (nurses and doctors) will be responsible for recruiting patients. At first, the screening will be carried out on the online platform which will coincide with the first call of the conventional protocol, where it will be assessed if the patient meets the inclusion and exclusion criteria. If the patient meets the inclusion and exclusion criteria, the system will allow the baseline visit to be made, which will coincide with the first call after the patient is diagnosed with COVID-19. Data from the initial visit will be recorded, the new patient will be registered with an associated mobile phone number and an anonymous and unique ID will be provided. The online platform itself will randomly assign the patient to the case or control group. At that point, a message will be sent to activate the patient. Once the user opens the message, they will have to click on the link to download the health application called ‘‘Home app’’ where they will fill in their data, receive information about the project and data processing and sign the informed consent if they agree. In the case of the active group, a request will be sent, with the delivery address of the bracelet, to the transport company that previously arranged the shipment of the devices. Once the patient receives the bracelet, they will link the bracelet to the application and if they need support, they will receive it either via telephone call, which will be available for 14 h a day, or in the application itself. Healthcare professionals will be able to record on the web panel the registered telephone calls made according to the current protocol, the vital signs will be displayed in real-time, the responses that will be provided three times a day from patients on their perceived clinical state, and the alerts issued by the alteration of any parameter. In the event of a serious alarm, it will be received by the emergency system to provide immediate care, if required by the patient. At the end of the monitoring period, the primary health care staff will discharge the patient. In the case of the active group, the logistics will be activated to collect the devices and take them to a disinfection point. In addition, to improve the healthcare support system, a satisfaction survey and a usability survey will be carried out among patients and healthcare professionals who have participated in the study.

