### 2.6. Patient and Public Involvement

Patients will actively participate in the study by reporting their symptoms three times a day and answering a series of verification questions when significant alterations in any of the monitored vital signs are detected (the latter only for patients in the active group). In addition, at the end of the study, both patients and participating healthcare professionals will be asked to complete a satisfaction and usability survey (SUS) to report on difficulties encountered with the Home app/online platform and areas for improvement.

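### The stated usability survey covers the app and platform but not the smartwatch and oximeter, and its date is late and not tied to the end of use

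*Protocol article*

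**What the plan says.** The Introduction of the protocol article lists among the secondary outcomes "the satisfaction of professionals and patients with the project and the usability of the technologies used in the project".

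**What is rated.** Section 2.5.3 applies the Spanish SUS to the Home app. Section 2.6 asks patients and professionals "to report on difficulties encountered with the Home app/online platform and areas for improvement". Section 2.5.1 also announces a satisfaction survey and a usability survey, without saying what the usability survey rates. It describes the system under evaluation as the application together with the wearable devices. Section 2.5.2 states that the devices are all that separates the two arms.

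**When it is rated.** Section 2.2 ends home use "after seven or ten days depending on symptomatology". Patients may then delete the app "from their mobile phone and stop wearing the monitoring devices". Section 2.5.1 adds that, in the active group, "the logistics will be activated to collect the devices and take them to a disinfection point" when monitoring ends. For the patient survey, section 2.5.3 says "patients will be contacted by telephone after the end of the study to complete surveys on their satisfaction", and section 2.6 places it at the end of the study.

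**The concern.** There are two separate problems.

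- **Object.** The outcome refers to technologies in the plural, but the stated instrument is directed at the app and platform. Both arms use the app. How patients found the watch and the oximeter, the component that is randomised, has no stated score.
- **Timing.** Patients rate something they stopped using well before, and active-arm patients no longer have the devices in hand. Recall error grows with the delay, and so does the number of patients who cannot be reached. Because the end of the study can be read in several ways, the recall interval is not fixed either.

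A usability rating taken close to use cannot be recovered once the devices have gone back and time has passed.

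**Working it through.** The plan gives no figure to reproduce here. The check compares the text on the object rated and applies date arithmetic to the timing.

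**Object rated**

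| Place in the protocol article | Object |
|---|---|
| Introduction, secondary outcomes | "the usability of the technologies used in the project" |
| 2.5.1, system modules | satisfaction and usability surveys, object not limited |
| 2.5.3 | Home app (SUS); satisfaction with taking part in the study |
| 2.6 | Home app and online platform |

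Both places that name a usability object leave out the smartwatch and oximeter. The one place that leaves the object open adds no device rating.

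**Timing inputs**
- End of use: day 7 or day 10 (2.2).
- Inclusion: up to 6 days after the positive diagnosis (Table 1).
- Candidate end dates: day 30 final visit (2.5.3); six months after the positive test (2.2), taken as 183 days (assumption); a negative second test, with no day given (2.5.3).

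**Formula.** Gap = end date − day of last use.

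Quarantine days counted from the positive test:
- Day 30: 30 − 10 = 20 days; 30 − 7 = 23 days.
- Six months: 183 − 10 = 173 days; 183 − 7 = 176 days.

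Quarantine days counted from inclusion at the 6-day limit, so that last use falls on day 10 + 6 = 16 or day 7 + 6 = 13:
- Day 30: 30 − 16 = 14 days; 30 − 13 = 17 days.
- Six months: 183 − 16 = 167 days; 183 − 13 = 170 days.

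Negative second test: no gap can be computed.

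Section 2.5.3 places the survey after the end of the study, so under the day-30 and six-month readings these are minimum gaps. They compare with 7 to 10 days of use.

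**The case against.** A reader might infer that usability goes unmeasured for the intervention as a whole. The documents do not support that. The app and platform belong to the evaluated system, and both are rated.

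Nor is a between-arm SUS comparison empty. In the active arm the app is where the devices are linked, oximeter values are entered and alarms are verified. A randomised difference in the app score therefore reflects the addition of the devices, though only indirectly. It is not a device score.

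It would also go too far to say that no active-arm patient will rate the devices. Section 2.5.1 leaves the object of the usability survey open. Questionnaire content is not shown, and an article may leave it to the full protocol. Satisfaction with taking part could include the experience of wearing the devices. What stands is that the named SUS object is narrower than the named outcome.

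On timing, an end-of-study survey is not an error in itself. Twenty days is not a firm minimum, because the negative-test reading could shorten the gap. Section 2.2 only permits patients to delete the app ("they will be able to remove the healthcare application called"); it does not say that they all do. Deletion and device return do not apply to the professionals who are surveyed.

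A reader might also infer strong selection against patients who progressed. No response rate or recall-error figure is given, so its size is unknown. No schedule reaches patients who died, and an in-app form alone would miss those hospitalised before discharge. This limits what moving the survey can achieve and is a reason to keep the telephone route.

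**Conclusion.** The point holds in a limited form. The stated SUS object is narrower than the secondary outcome and omits the smartwatch and oximeter, the only component that differs between the arms. The patient survey is late and has no single date:

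- about 20 to 23 days after last use on the day-30 reading (about 14 at the least if quarantine runs from inclusion);
- about 173 to 176 days on the six-month reading;
- undefined on the negative-test reading.

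These figures assume 183 days for six months and that use stops at day 7 or day 10. The consequence is avoidable recall error and non-response, of unknown size, in one secondary outcome. The primary analysis is not affected. The change is worth making because it is cheap and lets the trial answer its own usability question.

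**What to change.** - Align the Introduction, section 2.5.3 and section 2.6 on which technologies are rated, and fix one survey date relative to the end of use.
- Give the patient SUS and satisfaction survey in the app at the primary-care discharge step in section 2.5.1, before the app is removed and the devices are collected.
- In the active arm, add a SUS that names the smartwatch and oximeter.
- Keep the telephone survey as a full alternative for non-responders, for patients who stopped using the app early and for those hospitalised before discharge. Record the date of each response so that late answers can be identified.

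**Cost.** Protocol wording, one more in-app form, and about ten more items for active-arm patients. The discharge step and the telephone contact are already in the plan.
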